## Abstract

**Background:**

Previous studies have demonstrated the efficacy of rehabilitation after a cardiovascular procedure. Especially older and multimorbid patients benefit from rehabilitation after a cardiac procedure. Prehabilitation prior to cardiac procedures may also have positive effects on patients’ pre- and postoperative outcomes. Results of a current meta-analysis show that prehabilitation prior to cardiac procedures can improve perioperative outcomes and alleviate adverse effects. Germany currently lacks a structured cardiac prehabilitation program for older patients, which is coordinated across healthcare sectors.

**Methods:**

In a randomized, controlled, two-arm parallel group, assessor-blinded multicenter intervention trial (PRECOVERY), we will randomize 422 patients aged 75 years or older scheduled for an elective cardiac procedure (e.g., coronary artery bypass graft surgery or transcatheter aortic valve replacement). In PRECOVERY, patients randomized to the intervention group participate in a 2-week multimodal prehabilitation intervention conducted in selected cardiac-specific rehabilitation facilities. The multimodal prehabilitation includes seven modules: exercise therapy, occupational therapy, cognitive training, psychosocial intervention, disease-specific education, education with relatives, and nutritional intervention. Participants in the control group receive standard medical care. The co-primary outcomes are quality of life (QoL) and mortality after 12 months. QoL will be measured by the EuroQol 5-dimensional questionnaire (EQ-5D-5L). A health economic evaluation using health insurance data will measure cost-effectiveness. A mixed-methods process evaluation will accompany the randomized, controlled trial to evaluate dose, reach, fidelity and adaptions of the intervention.

**Discussion:**

In this study, we investigate whether a tailored prehabilitation program can improve long-term survival, QoL and functional capacity. Additionally, we will analyze whether the intervention is cost-effective. This is the largest cardiac prehabilitation trial targeting the wide implementation of a new form of care for geriatric cardiac patients.

**Trial registration:**

German Clinical Trials Register (DRKS; http://www.drks.de; DRKS00030526). Registered on 30 January 2023.

**Supplementary Information:**

The online version contains supplementary material available at 10.1186/s13063-023-07511-w.

## Administrative information

**Table Taba:** 

Title {1}	Prehabilitation in older patients prior to elective cardiac procedure (PRECOVERY): study protocol for a randomized, controlled, longitudinal, multicenter, two-arm, assessor-blinded trial
Trial registration {2a and 2b}	German Clinical Trials Register (DRKS; http://www.drks.de) (DRKS00030526)
Protocol version {3}	V3.0 from 27^th^ of March 2023
Funding {4}	Grant 01NVF21109 of the “Innovationsausschuss” of the German Federal Joint Committee (G-BA)

## Introduction

### Background and rationale {6a}

In 2050, one out of six persons (about 13.6 million people) in Germany will be 75 years or older [1]. With increasing age, the focus of medical care shifts to the maintenance of quality of life (QoL) and functional capacity, which enables older persons to care for themselves as long as possible. A threat to QoL and functional capacity of older individuals are cardiovascular diseases, such as coronary heart disease and degenerative diseases of the heart valves. These cardiovascular diseases will increase in prevalence and incidence as demographic changes occur [2]. Survival rates after cardiac procedures are increasing despite rising age and the associated increase in concomitant diseases. Essential for the high survival rate is the continuous advancement in cardiac medicine and the establishment of gentler interventional procedures [3]. Nevertheless, frail patients with reduced muscle mass, strength, and endurance have a threefold increased risk of postoperative morbidity and mortality [4, 5]. Older cardiac patients also have a significantly increased risk of suffering a cerebrovascular or cardiac event during or after surgery [6]. Especially in geriatric patients, decreased exercise capacity and loss of physical functioning before, during, and after hospitalization have a strong negative impact on QoL, self-determination and everyday resilience [7].

Cardiac interventions are often followed by a long period of convalescence. Postoperative/ postinterventional delirium occurs in 12 to 53% of patients and is associated with a poor long-term outcome in terms of nursing home admission, cognitive decline, reduced independence in daily life, and increased mortality risk [8]. In frail or delirious patients, mortality is up to 40% [9, 10]. It is clear, that older cardiac patients are in need of additional support in order to ensure that their QoL and functional capacity can be maintained—or even improved—after a cardiac procedure. One form of additional support for older patients is a preparatory program, so-called multimodal prehabilitation, which seeks to improve functional capacity, psychological and physical health prior to the cardiac procedure [11].

Currently, there are five systematic reviews with meta-analyses examining the effect of exercise-based prehabilitation prior to cardiac procedures [12–16]. These publications show that exercise-based prehabilitation can shorten the hospital stay [12, 13, 16], improve functional capacity measured by 6-min walking test [12], and reduce various postoperative complications [12, 14–16] such as atrial fibrillation [12] or pulmonary complications [14–16]. However, high heterogeneity of the included studies regarding the therapeutic interventions, the detected outcome parameters, and the cohorts included limit the validity of these findings. A recently published scoping review came to same conclusion [11]. The authors summarized that the evidence is supportive of prehabilitation before cardiac procedures in older and frail individuals but there is a need for an adequately powered, randomized, controlled, assessor-blinded intervention trial to assess the benefit of prehabilitation in improving outcomes in older and frail patients [11]. Especially high-quality multicenter prehabilitation studies prior to an elective cardiac procedure are needed.

Prior to elective cardiac procedures, patients are good candidates for a prehabilitation intervention because of their often advanced age, sometimes long waiting times, and already existing reduced exercise capacity [17]. However, there is no structured cardiac prehabilitation program in Germany that is tailored to the needs of this patient group, and is coordinated across the healthcare sectors.

This intervention trial aims to fill the above described scientific gap. PRECOVERY (Prehabilitation “Karl-Heinz” focusing on cardiac and cognitive functions prior to the cardiac procedure: an analysis of the health status) will evaluate the clinical and health economic effectiveness of prehabilitation in older patients prior to an elective cardiac procedure in a multicenter, two-arm, outcome assessor-blinded randomized controlled trial, comparing the efficacy of a prehabilitation program with standard medical care (SMC). In Germany, SMC for these patients means that they remain at home until the planned cardiac procedure with general instructions (e.g., optimized medication plan) and the opportunity to contact their primary care physicians or cardiologists if they experience physical discomfort. After hospital discharge, all patients have the opportunity to participate in a 3-week in- or outpatient cardiac rehabilitation program that is integrated into the German healthcare system.

Patients will be followed up at intervals for a year after the cardiac procedure, in order to determine the effects of the prehabilitation intervention on 1-year mortality, QoL, and functional capacity, as well as other factors relating to clinical and health economic outcomes.

### Objectives {7}

The objective of this randomized controlled trial (RCT) is to evaluate the efficacy of a 2-week inpatient multimodal prehabilitation intervention called “Karl-Heinz” (*K*ognitiv & k*a*rdiale P*r*ehabilitation vor *He*r*zin*terventionen [cognitive and cardiac prehabilitation prior to cardiac procedures]) for patients aged 75 years or older undergoing elective cardiac procedure (e.g., coronary artery bypass graft surgery or transcatheter aortic valve replacement).

The primary research question is as follows:

Does participation in the “Karl-Heinz” intervention lead to improvements in the co-primary endpoints (QoL/health status and mortality after 12 months) compared with SMC?

The secondary research question is as follows:

Does participation in “Karl-Heinz” lead to improvements in daily function, cardiopulmonary fitness, anxiety and depression, cardiac-specific QoL, and cognition? Additionally, the question if the intervention is associated with reduction of healthcare costs after 12 months compared with SMC will be addressed.

The explanation of further endpoints can be found in the study protocol [see Additional file 1].

### Trial design {8}

PRECOVERY is a confirmatory, randomized, controlled, two-arm parallel group, assessor-blinded multicenter intervention trial. If positive, we will confirm the efficacy of the multimodal prehabilitation intervention with regard to patients’ QoL, medical, cognitive, and psychosocial outcomes 12 months after an elective cardiac procedure. We will randomize 422 patients aged 75 years or older scheduled for an elective cardiac procedure to either (a) SMC (*n* = 211) or (b) a 2-week multimodal prehabilitation intervention (“Karl-Heinz”, *n* = 211) with an allocation ratio of 1:1 per hospital, patient’s age and gender with a follow-up period of 12 months. An additional component of the RCT is a detailed health economic analysis by the Department of Health Economics and Health Services Research, University Medical Center Hamburg-Eppendorf, Germany. Furthermore, an independent process evaluation in a mixed-methods design will be provided by the Department of General Practice of the University Medical Center Goettingen, Germany.

The primary aim is to demonstrate superiority of the intervention group compared to SMC group in terms of QoL and mortality 12 months after the cardiac procedure. The secondary aim is to show the superiority of the intervention group compared to the SMC group in terms of functional and cognitive capacity, heart-specific QoL, and activities of daily living after 12 months.

For the health economic analysis, we anticipate at least equivalence, a better non-inferiority in healthcare costs after 12 months in the intervention group compared to SMC group.

## Methods: participants, interventions, and outcomes

### Study setting {9}

In this study, a new form of care for older heart patients is being implemented in partnership with a large German health insurance company, AOK Lower Saxony. Nine German departments for cardiac surgery and/or cardiology will recruit patients (primarily those who are insured by the AOK Lower Saxony) scheduled for an elective cardiac procedure. The 2-week multimodal prehabilitation intervention “Karl-Heinz” will be provided in seven inpatient cardiac-specific rehabilitation hospitals, and one outpatient rehabilitation hospital (prehabilitation centers).

A current list of all participating clinics and prehabilitation centers, as well as all scientific partners, can be found online at the project homepage (https://herzzentrum.umg.eu/precovery/). Likewise, in the supplemental material is a German and English version of the study protocol. The flow diagram of the study is presented in Fig. 1.

**Fig. 1 Fig1:**
[figure not shown]
PRECOVERY flowchart. Abbreviations. CP = cardiac procedure; OPS = operation and procedure codes; SMC = standard medical care

### Eligibility criteria {10}

We will include patients 75 years or older undergoing elective cardiac procedures defined by the German operation and procedure codes catalog (OPS, see Table 1). Due to legal reasons to the project funding participation of patients included in Lower Saxony is limited to patients of AOK Lower Saxony public health insurance provider.

**Table 1 Tab1:** Explanation of the translated OPS Code

OPS Code and Procedure
5–35: Operations on heart valves and septa as well as on vessels close to the heart
5–351: Replacement of heart valves with prostheses
5–352: Change of heart valve prostheses
5–353: Valvuloplasty
5–354: Other operations on heart valves
5-35a: Minimally invasive surgery on heart valves
5–36: Coronary artery surgery
5–360: Desobliteration (endarterectomy) of coronary arteries
5–361: Creating an aortocoronary bypass
5–362: Creating an aortocoronary bypass using minimally invasive technique
5–363: Other revascularization of the heart

*Abbreviations OPS* operation and procedure codes

An adapted recruitment strategy has been developed as an option for the case that the number of eligible ≥ 75 years old AOK-insured persons is not adequate to reach our recruitment goals. First, the age requirement will be lowered by 10 years to include all retired persons ≥ 65 years. PRECOVERY is powered to EQ-5D-5L with a minimal clinically relevant effect. Current literature shows a positive effect of prehabilitation on QoL also in patients who are ≥ 53 years of age [18, 19]. The costs for prehabilitation are covered by the health insurance for retired persons; however, the pension fund is responsible for such costs for employed persons. Therefore, PRECOVERY is only open to retired persons. Second, by continued recruitment problems the study will be opened to include members of all health insurance companies.

Inclusion and exclusion criteria are summarized in Table 2.

**Table 2 Tab2:** PRECOVERY inclusion and exclusion criteria

**Inclusion criteria**
Age ≥ 75 years
Planned elective cardiac procedure (OPS: 5–351 to 354, 5-35a, 5–360 to 363)
Sufficient independence, ability to care for self and participate in prehabilitation
Insurance status of all patients from Lower Saxony to patients of AOK (public health insurance provider)
Ability to give consent
Willingness to participate voluntarily in the study after informed consent with signed consent form
Ability to speak, read, and understand German
**Exclusion criteria**
Lack of capacity to consent
Katz index 0
Need for treatment in an acute care hospital
Severe dementia or severe mental disorders, acute delirium
Diagnosis of acute alcohol or drug abuse
Unstable angina pectoris
Heart failure, NYHA IV
Myocarditis, hypertrophic obstructive cardiomyopathy, main stem stenosis ≥ 80%
Severe refractory cardiac arrhythmias
Recent aortic dissection
Peripheral arterial occlusive disease stage ≥ III according to Fontaine
Symptomatic carotid stenosis or carotid stenosis requiring therapy
Renal insufficiency requiring dialysis
Hepatic insufficiency, child B and child C
Advanced (metastasized) oncological disease
Neurological, orthopedic or rheumatic comorbidities that militate against physical training
Participation in another intervention study (participation in registry studies is allowed)

*Abbreviations *
*OPS* operation and procedure codes, *NYHA* New York Heart Association

### Who will take informed consent? {26a}

Prior to baseline assessment, eligible patients and their relatives will be informed about the study goals, duration of the study, the role of each participant, randomization, and any risks in written and oral forms. After written informed consent from patients, and their relatives by a study physician, baseline assessment (t0) will take place and patients will be randomized (t1). Original patient information and consent forms are available on request from the corresponding author. If a patient does not have any relatives, then persons close to him or her can be consulted. Participation in the study is also possible without relatives or close persons.

### Additional consent provisions for collection and use of participant data and biological specimens {26b}

Enrolled participants are offered the opportunity to participate in a voluntary sub-study where biological samples will be analyzed. This specific research topic in the study population is not covered by the grant of this trial.

## Interventions

### Explanation for the choice of comparators {6b}

The “standard medical care” comparator appears to be the appropriate option for a pragmatic effectiveness analysis. The control group will receive an information folder with general information and SMC provided as part of the cardiac procedure process.

### Intervention description {11a}

In contrast, the intervention group will receive a 2-week individualized prehabilitation program “Karl-Heinz” prior to the elective cardiac procedure. Study participation will have no influence on perioperative processes.

### Prehabilitation

Patients in the intervention group receive a 2-week preventive, intensive, and full-day prehabilitation in selected cardiac-specific rehabilitation facilities (prehabilitation centers) for targeted, holistic preparation for the cardiac procedure. Prehabilitation comprises a multimodal, interdisciplinary therapeutic approach individually adapted to the patients’ needs in order to achieve the best possible physical and mental health status with improved functional reserve prior to the planned cardiac procedure. The prehabilitation program “Karl-Heinz” includes seven modules: (1) sports and exercise therapy, (2) occupational therapy, (3) cognitive training, (4) psychosocial support, (5) disease-specific education, (6) informative talks with relatives, and (7) special hygiene training/nutritional intervention [details see Additional file 3].

To standardize the prehabilitation program, a treatment manual [details see Additional file 3] and a minimum of therapy requirements (see Table 3) was designed in a multidisciplinary team from all participating centers and the two participating health insurance companies (AOK Lower Saxony and AOK Baden-Württemberg). Based on this, a train-the-trainer concept with detailed standard operating procedures (SOPs) and additional training videos was created. All coordinating team members of each prehabilitation center (the so-called “multipliers”) will receive 2 days of train-the-trainer instruction on the individual modules of the treatment manual “Karl-Heinz”. These persons are trained to perform their tasks as “multipliers” a few weeks before the first patient is enrolled.

**Table 3 Tab3:** Overview of the minimum of therapy requirements during prehabilitation program “Karl-Heinz”

**Form of therapy**	**Minimum of requirements**
(1) Sports and exercise therapy	Scope: 1 active unit per day (5 × per week) of 30 min each
	Content: endurance, strength/flexibility, coordination training
(2) Breathing therapy	Scope: 3 times per week of 30 min each
	Content: Group setting with daily self-training
(3) Occupational therapy	Scope: 2 times per week of 30 min each
	Content: see exercise therapy plus tips for the sustainability of prehabilitation
(4) Cognitive training	Scope: 2 times per week of 30 min each
	Content: attention and concentration training
(5) Psychosocial intervention	Scope: 2 times during prehabilitation period
	Content: Delirium education, preparation for surgery inclusive procedures in the hospital and PMR
(6) Disease-specific education	Scope: 3 units in the prehabilitation period, video training if necessary
	Content: sleep, nutrition, exercise, risk factors, mindfulness, social counseling
(7) Informative talks with relatives	Scope: 1 time during the prehabilitation period
	Content: see treatment manual in the additional file 3

Subsequently, on-site training sessions will be conducted by the multipliers for the intervention staff of the respective prehabilitation centers. The individual elements of the “Karl-Heinz” prehabilitation are not new, but the embedding of a heart-specific program in a structured trans-sectoral concept represents a previously unaddressed need in the care of older patients.

The initial assessment of the individual exercise capacity is carried out by the responsible physicians of the prehabilitation center. Experienced therapists are in regular exchange with the medical staff to individually increase the exercise intensity depending on the primary cardiac disease.

The contents of the individual training interventions are based on current study results, surveys of the participating prehabilitation centers, and interviews with experts. Due to the limited number of studies and the high heterogeneity of existing prehabilitation training intervention studies in cardiological patients, the design of the training forms was based on existing secondary prevention recommendations for cardiological sports and exercise therapy [20–22].

### Criteria for discontinuing or modifying allocated interventions {11b}

During the prehabilitation intervention, the supervising study physicians of the prehabilitation center will obtain feedback on the participants’ treatment experience minimum twice weekly during medical rounds. Therefore, the multimodal prehabilitation intervention can be adjusted at any time if necessary.

Adverse events (AEs) including serious adverse events (SAEs) will be documented in the medical record and transmitted to the recruiting center prior to the cardiac procedure. The cardiovascular AEs in form of major cardiac events (MACE) and predefined SAEs will be documented into the secuTrial® electronic database from the medical record after the prehabilitation intervention. To ensure blinding of study assessors, a non-blinded study investigator will fill cardiovascular AEs and SAEs of patients in the SMC and intervention group into the secuTrial® database at t2. An independent Data Safety Monitoring Board (DSMB) including national and international experts on cardiology, cardiac surgery, geriatrics, cardiac rehabilitation, prehabilitation, and patient advocates has been established. The DSMB reviews the cardiovascular AEs and SAEs of the prehabilitation intervention and SMC before the cardiac procedures on a quarterly basis and determines whether the safety of the patients is still ensured and whether the continuation of the study without any changes is justifiable, or—if necessary—makes recommendations for discontinuation or modifications of the study. To fulfill this task, the DSMB receives information about protocol deviations, the status of patient recruitment and the observed cardiovascular AEs and predefined SAEs.

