Thirty-day mortality, length of stay in intensive and normal care unit, AE/SAE assessment, hand strength measured by Marin-Vigorimeter [35, 36], functional capacity collected by the 6-min walk test [37], bioelectrical impedance analysis to elevate body composition [38], Mini Nutritional Assessment to detect malnutrition [39, 40], Pittsburgh Sleep Quality Index to detect sleep quality [41–43], Maastricht Questionnaire to evaluate the vital exhaustion [44, 45], Informant Questionnaire on Cognitive Decline in the Elderly to assess opinion of relatives (IQCODE; [46]; Zarit Burden Interview to measure burden of relatives (G-ZBI; [47]), Clinical Frailty Scale to assess frailty (CFS; [48]), American Thoracic Society (ATS) scale to evaluate dyspnea (dyspnea scale of the ATS; [49]), self-reported subjective memory impairment (SMI; [50]) to measure patients’ opinion about the own memory performance, Selbstwirksamkeits-überzeugung ([general self-efficacy scale], SWE) scale to identify self-efficacy expectancy [51–53], Hamburger Fragebogen zum Krankenhausaufhalt [Hamburg Questionnaire on Hospital Stay] to assess patients’ satisfaction with the hospital stay [54], optimism measured by Life-Orientation-Test revised (LOT-R; [55]), loneliness detected by UCLA Loneliness Scale [56, 57], illness perception measured by Illness Perception Questionnaire (IPQ; [58]), treatment expectancy measured by Treatment Expectation Questionnaire (TEX-Q; [59]), and institutionalization/dependence on care assessed in Clinical data / sociodemographic interview.

The mixed-methods process evaluation will evaluate intermediate outcomes (dose, reach, fidelity, adaptions) of the intervention [60]. It assesses the implementation of the prehabilitation itself and the reactions and perspectives of involved persons. Moreover, barriers and facilitating factors will be explored [61]. More details will be published in a separate study protocol.

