### Frequency and plans for auditing trial conduct {23}

An independent member of the Clinical Trials Unit of the University Medical Center Goettingen will act as a monitor and regularly review the recruitment centers. After a site initiation visit, the monitor will visit once a year the recruitment facilities and conduct an interim visit. The monitor will review documentation of AEs and SAEs, patient and study records. Prehabilitation centers will be monitored indirectly by reviewing medical records sent to recruitment centers after prehabilitation by monitor. During the first year of the intervention, prehabilitation centers will be visited by a consortium team member for follow-up as well as refresher training in the “Karl-Heinz” treatment manual.

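### Pre-procedure events in the intervention arm come from a supervised facility record and no equivalent source is named for controls, so the AE/SAE comparison that the DSMB reviews is at risk of detection bias

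*Protocol article*

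**What the plan says.** **Intervention arm.** Section {11b} says that AEs, including SAEs, "will be documented in the medical record and transmitted to the recruiting center prior to the cardiac procedure". MACE and predefined SAEs then "will be documented into the secuTrial® electronic database from the medical record after the prehabilitation intervention". Section {23} shows which record is meant: "Prehabilitation centers will be monitored indirectly by reviewing medical records sent to recruitment centers after prehabilitation by monitor". Under the intervention description {11a}, the program lasts two weeks and is full-day. During it the supervising physicians "will obtain feedback on the participants’ treatment experience minimum twice weekly during medical rounds" ({11b}).

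**Control arm.** Section {6a} says of standard medical care that "they remain at home until the planned cardiac procedure with general instructions", with "the opportunity to contact their primary care physicians or cardiologists if they experience physical discomfort". No scheduled contact between randomisation and t2 is described, and no source document for events is named.

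**Both arms.** Under {11b} a non-blinded investigator enters the events of both groups at t2. Section {22} applies one recording rule to all patients from randomisation, and Table 4 schedules AE/SAE at t2 for everyone.

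**Use.** The DSMB "reviews the cardiovascular AEs and SAEs of the prehabilitation intervention and SMC before the cardiac procedures on a quarterly basis" ({11b}) and on that basis advises on continuation or modification. "AE/SAE assessment" is also listed among the further endpoints in {12}.

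**The concern.** A comparison of event counts is fair only if an event of a given kind has the same chance of being noticed in each arm. Here one arm is seen by cardiac-rehabilitation staff every treatment day and by a physician at least twice a week, and what they see is written down and forwarded. In the other arm an event becomes known only if the patient seeks help or mentions it at t2.

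A brief arrhythmia or a short episode of chest symptoms may be noted in the first setting and never recorded in the second. With equal true risk, the intervention arm would then show more events. This is the comparison from which the DSMB judges whether prehabilitation is safe before the procedure, so an excess that arises only from closer observation could prompt an unwarranted recommendation. It could also enter the published safety results as apparent harm.

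**Working it through.** The article states no pre-procedure event rate, detection share or DSMB threshold, so there is no plan figure to reproduce. The check has two parts.

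**1. The two arms side by side**

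| | Intervention | Control |
|---|---|---|
| Setting before the procedure | Full-day facility care for 2 weeks ({11a}), otherwise not described | Home ({6a}) |
| Medical contact | Physician rounds at least twice weekly ({11b}) | Initiated by the patient ({6a}) |
| Named source of events | Facility record sent to the recruiting centre ({11b}, {23}) | None named |
| Entry | Non-blinded investigator at t2 ({11b}) | Same |
| Start of recording | Randomisation ({22}) | Same |

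The last two rows are equal. They govern what is recorded, when and by whom. The first three rows govern whether an event is found at all, and these differ.

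**2. How large the effect could be (illustration on assumed detection shares)**

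Inputs from the article: 2 weeks of supervision; patients are recruited 4-6 weeks before the procedure ({15}); 211 per arm ({8}).

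Assumptions: equal true risk in both arms, events spread evenly over the wait, detection of 95% while supervised, and detection d of 60% to 80% at home in either arm.

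Supervised share of the wait: f = 2/6 = 1/3 to 2/4 = 1/2.

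Intervention detection = f × 0.95 + (1 − f) × d. Control detection = d. Apparent risk ratio = the first divided by the second.

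| d | f | Intervention detection | Apparent ratio |
|---|---|---|---|
| 0.60 | 1/3 | 0.317 + 0.400 = 0.717 | 0.717 / 0.60 = 1.19 |
| 0.60 | 1/2 | 0.475 + 0.300 = 0.775 | 0.775 / 0.60 = 1.29 |
| 0.80 | 1/3 | 0.317 + 0.533 = 0.850 | 0.850 / 0.80 = 1.06 |
| 0.80 | 1/2 | 0.475 + 0.400 = 0.875 | 0.875 / 0.80 = 1.09 |

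In counts, with an assumed true risk of 10%, each arm has 211 × 0.10 = 21.1 true events. In the most unequal case 21.1 × 0.775 = 16.4 are seen against 21.1 × 0.60 = 12.7, an excess of about four. In the least unequal case 21.1 × 0.850 = 17.9 are seen against 21.1 × 0.80 = 16.9, an excess of about one.

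As d approaches 0.95 the ratio approaches 1. That is the plausible situation for death and hospitalised MACE.

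**3. Event scope**

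The extraction step in {11b} covers MACE and predefined SAEs. Section {22} asks for all adverse cardiovascular events, revascularisations, other invasive cardiac interventions and all SAEs. The wider list includes events whose detection depends more on observation, so the size of the problem depends on which scope is applied.

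**The case against.** The case on the other side is substantial, and much of it stands.

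- **Common entry and a common rule.** The same type of investigator enters both arms at t2, and {22} sets one rule from randomisation. This is correct, and it means that the window is already largely fixed. It does not settle the point, because the investigator can enter only what someone has found.
- **Hard events.** What {11b} extracts from the facility record is MACE and predefined SAEs, which depend less on supervision than minor events do. This narrows the concern but does not remove it, because {22} is wider.
- **A condensed article.** The full protocol is a supplement that was not available here, and it may name a source for control events. If so, a sentence of clarification answers that part. The article itself, however, fixes a source that only one arm can supply.
- **Limited consequence.** AE/SAE is neither a co-primary nor a secondary endpoint, the article states no numerical safety threshold, and the DSMB includes prehabilitation and rehabilitation experts who can allow for closer observation. This stands. They can allow for it more reliably if the tables show which events came only from the facility record.

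A reader might infer three stronger things that the documents do not support:

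- **That control patients have no record.** The article only fails to name one. Controls may see their own physicians, and they attend t2.
- **That recording in the intervention arm stops at discharge from prehabilitation**, so that later events before the procedure are lost. The wording in {11b} says when the record is used, not when observation ends, and both the t2 entry and {22} point the other way.
- **That the comparison is shown to be biased.** Without detection shares, only the risk can be stated.

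**Conclusion.** The point holds as a risk of detection bias in the pre-procedure AE/SAE comparison. It rests on what the article states: a supervised facility record as the source in one arm, patient-initiated contact and no named source in the other, and a DSMB review across both.

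The direction would tend to be an apparent excess in the intervention arm, mainly for cardiovascular events short of death or hospitalised MACE. The size is unknown. The range of 1.06 to 1.29 depends entirely on the assumed detection shares, equal true risk and an even spread of events over a 4-6 week wait. It shrinks towards 1 as detection at home improves.

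The co-primary endpoints, their analysis and the sample size are not touched. The change is worth making because it is cheap and the comparison informs the judgement on continuing the trial. It does not put the trial's main conclusion in doubt.

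**What to change.** 1. State that the pre-procedure window runs from randomisation to t2 in both arms, as {22} and Table 4 already imply.
2. At t2, have the non-blinded investigator named in {11b} put the same structured event questions to every patient in both arms. Any hospital or physician contact should be documented in the same way. The prehabilitation record stays as an additional source.
3. Mark the source of each event. In the DSMB tables show death and MACE first, and list separately the events known only from the prehabilitation record.
4. Reconcile the event scope of {11b} with that of {22}, so that it is clear which events are entered and which the DSMB receives.

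The cost is one common t2 form, a changed table layout and a few minutes per patient for an investigator who already makes the entry. Some difference in surveillance will remain, because it is inherent in comparing supervised care with waiting at home. The separate listing makes that difference visible but does not remove it.
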